**Women’s Health Advocate**

7. [name]

The DSMB originally included [name], a women’s health advocate from South Africa. However, [name] withdrew herself from the board just prior to the November 2005 meeting. [name] was replaced by [name] in October 2005.

The trial co-PIs, consulting statisticians, and data management team will consult with the DSMB, which will then be responsible for the following duties: creating a meeting schedule and format, determining the format for data presentation, specifying who will have access to interim data and who may attend all or part of the DSMB meeting, developing procedures for assessing conflicts of interest, overseeing the method and timing of the interim analysis, and organizing report preparation and distribution.

DSMB meetings will occur by telephone unless the chair requests a face-to-face meeting. All other communication with DSMB members will be by e-mail and teleconference. DSMB meetings will include an open session, in which overall trial conduct issues will be discussed. [name] and [name] or their designees and possibly other trial staff will attend the open session to answer questions and raise issues for the DSMB to consider. The other co-PIs will not be permitted to attend the closed session of the meeting when trial results are discussed.

Analyses and specific duties to be conducted by the DSMB are described in section 12.6.

## 5.4 Study Monitors

Study monitors provide quality assurance to the study. Because their reviews are independent as opposed to advisory, their duties are described below in Quality Assurance (section 14.3).

# 6 Study Population

## Study Sites

(Note that all sites did not begin the study at the same time; site-specific accrual is presented below, section 7.1.2.)

### Harare, Zimbabwe

In Zimbabwe, HIV prevalence among adults increased from about 9% in 1990 to an estimated 25% in 1999.20,21 A population survey of close to 10,000 people, fielded between 1998 and 2000, found that women aged 17 to 24 years were four times more likely to be HIV positive than were men of the same age.22 Recent UCSF studies based in Harare, the capital city, (see URL http://www.uz-ucsf.co.zw) observe prevalence rates of 38% and incidence rates of between approximately 3.5%- 5% a year throughout the reproductive age span.

The UZ-UCSF Collaborative Research Programme in Harare, Zimbabwe enjoys a long-standing relationship with several family planning and reproductive health clinics in and around Harare, Zimbabwe. These clinics serve urban and peri-urban women, many of who are appropriate candidates for participation in this trial.Our Zimbabwe site has a successful track record for enrolling several hundreds to thousands of women into large epidemiologic studies. This was the first site to begin the study with enrollment starting in September 2003. Women exiting their participation in other studies are among those recruited for this study. Likewise, staff including clinicians who are trained in counseling, testing and contraceptive counseling have transitioned into this study.

The recruitment areas identified for the MIRA study are Chitungwiza, a peri-urban suburb 30 km south of Harare, and Epworth, another Harare suburb approximately 25 km to the southeast that is slightly poorer and less developed than Chitungwiza. Enrollment of women began in Chitungwiza in September 2003 and in March 2004 at Epworth.

### Durban, South Africa

Durban is located on the Indian Ocean coast in the province of KwaZulu-Natal, the province in South Africa with the highest HIV incidence. Between 1999 and 2000, HIV prevalence among women in their twenties in KwaZulu-Natal grew from 32.5% to 36.2% and incidence rates greater than 10% have been reported in certain areas.23

Durban's surrounding areas are the base for two groups of women who together comprise one cohort. One is peri-urban, drawn from the Umkomaas region located 60 km south of Durban. The other is rural, drawn from the Bothas Hill area located 40 km west of Durban. It is important to include rural women in the study for generalizability and reasons related to public policy, even if the cost per woman is marginally higher. Scheduled study visits take place at the MRC clinic. Enrolment for this site began in November 2003.

Other current studies in communities of this nature in areas north of Durban have shown that community-based HIV prevalence is around 45%. We estimate the prevalence of HIV in areas south and west of Durban to be around 40%. We do not have incidence data in this research naïve population. However, taking the high prevalence of HIV in RSA and sero-prevalence data from young women in KwaZulu-Natal, we estimate that the incidence in child-bearing women in these communities is around 5%.24

### Johannesburg, South Africa

The Perinatal HIV Research Unit (PHRU), which is based at the Chris Hani Baragwanath Hospital in Johannesburg, South Africa, was selected as the third study site. Enrollment began at PHRU in March 2004. The study population is being recruited from Soweto, an urban African township in the province of Gauteng, 15 km to the southwest of Johannesburg, with a population estimated between 1.2-2 million people in an area of 63 km2. The PHRU has close links with all 23 of the Soweto Primary Health Care clinics, which provide reproductive health and primary care services, and has a daily presence in 13 of the clinics. For the MIRA trial, women are recruited from family planning and well-baby clinics and from the community in Soweto. The Unit has an established Community Advisory Board and VCT services in a range of settings in Soweto and counsels and tests over 28,000 people for HIV each year. The reported HIV prevalence rate in Gauteng Province among adults ages 15-49 was 22.2% in mid-2006.25

## 6.2 Eligibility Criteria

To be eligible for participation, a woman must satisfy the following criteria:

- Age 18 to 49 years old
- Sexually active (coital frequency at least four times per month on average)
- HIV-negative based on testing within 14 days prior to enrollment
- *Chlamydia trachomatis-* and *Neisseria gonorrhoeae*-negative based on testing within 30 days prior to enrollment or, if positive, completes treatment before enrollment
- Have a healthy cervix as assessed by naked-eye speculum exam at enrollment.
- Planning to live in the study area for the next 24 months
- Willing to be randomly assigned either to use or not use a latex diaphragm with lubricant gel during her participation in the study and to follow the protocol, including being tested for HIV and STIs
- Willing and able to give informed consent

## 6.3 Exclusion Criteria

The following criteria will exclude a woman from study participation:

- Known sensitivity or allergy to latex
- History of TSS (as suggested by current labeling for diaphragm use)
- Currently pregnant or desiring to become pregnant in the next two years
- No cervix (total hysterectomy)
- Refuses treatment for diagnosed or suspected current STI and/ RTI requiring treatment at enrollment
- Within six weeks of any pelvic surgery or last pregnancy outcome at the time of enrollment.
- Presence of clinically apparent lesion(s) with epithelial disruption at enrollment (may enroll after lesion(s) has healed, if otherwise eligible)
- Injected illicit drugs in the 12 months prior to screening and enrollment
- Blood transfusion or received blood products in 3 months prior to screening and enrollment
- Unable or unwilling to insert the diaphragm correctly
- Participation in any other clinical trial including those of a vaginal product or barrier contraceptive; verification by comparing participant lists to other concurrently running research studies may be conducted if necessary
- Unable to speak English, Zulu, Shona, or Sotho
- Other conditions that, in the opinion of the investigator, would constitute contraindications to participation in the study or would compromise ability to comply with the study protocol, such as a major psychiatric disorder
- Does not meet eligibility criteria within 5 screening or 5 enrollment visits

# 7 Accrual, Follow-up, and Sample Size

## 7.1 Primary Endpoint

**7.1.1 Required sample size**

Sample size calculations are made by comparing HIV incidence rates between study arms using a log rank test stratified by study site and using approximate methods described by Lachin and Foulkes. 26We initially assumed that participants will be recruited over a period of 2 years, that the duration of the study would be 3 years, and that annual HIV incidence in the non-diaphragm arm (control group) would be approximately 4%, 5% and 3.5%at the Harare, Durban, and Johannesburg sites respectively. We further assumed that these sites would contribute 49%, 29%, and 22% of the total sample respectively and that discontinuation rates, including lost to follow up and true discontinuations, would not exceed approximately 7% per year at all sites or a total of approximately 20% over the three-years field implementation period. With these assumptions we required a total of 4500 women to have 90% power to detect a 33% treatment-related reduction in incidence as significant at the 5% level, assuming a two-sided alternative. This sample size and the assumption of constant rates of recruitment and censoring implies that approximately 4000 woman years of follow-up will be required per arm to detect a treatment-related reduction in incidence of 33%. This corresponds to a total of approximately 293 total serconversions in both arms combined. The following table presents enrollment goals and expected numbers of seroconversions by site.

**Table 4***: Approximate numbers of women to be enrolled to reach required number (293) seroconversions. We assume approximately 20% discontinuation rate at each site over the entire study period.*

|  | **Enrolled** | **Estimated annual incidence (overall)** | **Minimum estimated**  **Infections** |
| --- | --- | --- | --- |
| Harare | 2200 | 4% | 134 |
| Durban | 1300 | 5.0% | 99 |
| Johannesburg | 1000 | 3.5% | 60 |
| **Total** | **4500** | **~4.0%** | **293** |

If incidence is actually higher than assumed here, the diaphragm actually confers more than 33% protection, or the discontinuation rate is lower, it may be possible to end the study early. This decision will be made via stopping rules that will be considered during the interim analysis conducted by our DSMB (section 12.6. below).

In April 2005, the study statistician did a recalculation of the sample size based on actual HIV incidence rates to date. The overall annual incidence was found to be 3.5%. In order to maintain 90% power to detect a 33% reduction in HIV infection, it was estimated that 500 more women were needed in the trial, bringing the total sample size to 5000 women. Each site increased their target enrollments: Harare to 2500, Durban to 1500, and Johannesburg to 1000. In addition, re-calculations of the estimated number of infections and woman-years of data needed to detect a difference between study arms have produced higher figures. Thus while previous versions of the MIRA Technical protocol listed 280 incident infections needed, and 3500 woman-years of data per arm, we are now operating under the estimates of 293 incident cases and 4000 woman-years per arm.

The final enrollment numbers for the study sites were 2502 at UZ-UCSF, 1515 at MRC, and 1028 at PHRU. A total of 5045 women were enrolled in the study.

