# 2 Study Summary

**Study Purpose:** To determine the effectiveness of the diaphragm with Replens lubricant gel in the reduction or prevention of the heterosexual acquisition of HIV among women.

**Study Design:** Multi-site randomized, controlled, trial with two study arms:

1) Ortho All-Flex Arcing Spring latex diaphragm with Replens lubricant gel, and 2) a non-diaphragm and gel control arm.

Women in both arms receive male condoms, safer-sex counseling, and diagnosis and treatment of sexually transmitted infections.

**Sample Size:** 5,000 women (2,500 per arm) seen for an average of 18 months (range of 12-24 months of follow-up).

**Study Population:** HIV-negative, sexually active, non-pregnant women.

**Visit Schedule:** Screening, enrollment, two-week post-enrollment visit, and 4 to 8 quarterly visits depending on date of enrollment. Optional visits any time for counseling, obtaining additional supplies, or other concerns.

**Study Duration:** Approximately 48 months total, with 6 months for start up activities and 6 months for analysis and write-up.

**Primary Objectives:** To determine the effectiveness of the diaphragm with Replens

lubricant gel in preventing heterosexual transmission of HIV

among at-risk women.

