# 4 Study Objectives and Design

We are conducting a prospective, randomized, controlled, effectiveness trial of the diaphragm with lubricant gel at three sites, one in Zimbabwe and two in South Africa. We offer all women in the trial an HIV prevention package that includes HIV testing, safer sex counseling, free male condoms, and diagnosis and treatment of STIs. At each site, women are randomized into two groups. One of these groups receives latex diaphragms with Replens lubricant gel and counseling and training on how to use them while the other does not. We are following women quarterly for up to two years. We are measuring the incidence of HIV, cervical STIs (*Chlamydia trachomatis*, *Neisseria gonorrhoeae*), and other STIs (*Treponema pallidum*, *Trichomonas vaginalis*, and HSV-2), and will compare rates between the two groups. Because our main intervention of diaphragm with lubricant gel is offered as part of an HIV prevention package, we expect that HIV rates in both the intervention and control arms likely will be lower than those observed in the community at large. We took this into account in our sample size calculation.

We are enrolling 5,000 women who will be seen over a 12 to 24 month period, totaling approximately 7,000 woman-years of follow-up. This estimate was based on the expectations that there would be an average HIV incidence rate of 4%, that each woman we enrolled would participate on average 18 months, and that discontinuation rates would be 6-7% per year for a total of approximately 20% over the study period (3 years of field work). The expected discontinuation rates were based on on-going cohort studies at two of the sites and include true loss-to-follow-up (*i.e.* women who are lost and who have no outcome data). See section 7 below for sample size details and justification.

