## 12.6 DSMB analyses

The DSMB will review interim data when 100 HIV seroconversions (approximately one-third of the expected 293 infections) have been observed. Based on the advice of the DSMB, an additional interim analysis will be conducted when 195 HIV seroconversions (approximately two-thirds of the expected 293 infections) have been observed. They will tabulate events by study group, site, and woman-years of exposure.

The interim analyses will be performed using an O’Brien Fleming group sequential design. The assumptions used to determine sample size (*i.e.*, accrual, HIV seroincidence, and retention rates at each site) will be assessed and alterations to the overall sample size will be made if recommended by the DSMB. A consulting statistician will develop the DSMB data analysis plan in close collaboration with the co-PIs and data managers of the trial. However, the analyses will be conducted by the consulting statistician and his/her team without involvement of the co-PIs, data managers, any other trial investigators, or any other trial management staff.

The DSMB will also provide clear stopping rules and guidelines for other protocol modifications based on the interim results. The DSMB may also recommend other protocol changes. If interim results provide convincing evidence of safety concerns, significant benefit of diaphragm use, faster accumulation of trial endpoints than anticipated, or futility (*i.e.* a very low probability that the trial will ultimately demonstrate that the diaphragm is effective), the DSMB may recommend early termination of the trial. If interim results suggest that the incidence of trial endpoints is lower than anticipated, but there are no futility concerns, the DSMB may recommend increasing the total woman-years of follow-up. The DSMB may also recommend other protocol changes.

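### The 293 infections and 4,000 woman-years per arm behind the 90% power claim do not fit the 18-month mean follow-up and 7,000 woman-years stated elsewhere in the protocol

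*Protocol*

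**What the plan says.** Section 7.1.1 first assumes that women are "recruited over a period of 2 years, that the duration of the study would be 3 years". It takes control-arm incidences of 4%, 5% and 3.5% a year at Harare, Durban and Johannesburg, and loss of about 7% a year. On that basis "we required a total of 4500 women to have 90% power" to detect a 33% reduction "as significant at the 5% level, assuming a two-sided alternative". It attaches 4,000 woman-years per arm and 293 infections to this calculation, and Table 4 splits the 293 by site.

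The same section then reports a recalculation in April 2005: "The overall annual incidence was found to be 3.5" per cent, so 500 women were added to keep 90% power, and "we are now operating under the estimates of 293 incident cases and 4000 woman-years per arm".

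Section 2 describes "5,000 women (2,500 per arm) seen for an average of 18 months (range of 12-24 months of follow-up" months range included, and section 9.5 caps participation at 24 months. Section 4 states: "We are enrolling 5,000 women who will be seen over a 12 to 24 month period, totaling approximately 7,000 woman-years of follow-up". It pairs that total with an average incidence of 4% and a mean of 18 months.

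Section 12.6 sets the interim looks at 100 and 195 infections, the second described as "approximately two-thirds of the expected 293 infections".

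**The concern.** The woman-years said to be needed (8,000) exceed the woman-years said to be expected (7,000) from the same women. The infection target matches neither the follow-up and observed incidence nor the number that a 33% reduction requires at 90% power.

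These figures are in use. The 293 defines the one-third and two-thirds points of the O'Brien-Fleming looks. The 90% power is repeated in section 12.7.3. Section 12.6 also asks the monitoring board to reassess the sample-size assumptions, and a board comparing accruing data with section 7 would reach a different view from one using section 4.

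**Working it through.** **Inputs.** Hazard ratio 0.67 (section 12.7.3); two-sided 5%, 90% power, 7% annual loss and control rates of 4%, 5% and 3.5% with site shares of 49%, 29% and 22% (section 7.1.1); 1:1 allocation and an 18-month mean (section 2); 24-month cap (section 9.5); 3.5% overall incidence (section 7.1.1).

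**1. The plan's own figures.** I used exponential event and loss hazards, with loss hazard −ln(1 − 0.07) = 0.0726. Take 4,500 women, uniform 2-year accrual, a 3-year study and no cap on follow-up (12–36 months, mean 24). The site rates then give 3,988 and 4,045 woman-years per arm and 280 infections. A Lachin–Foulkes-type calculation at a 4% control rate gives 4,508 women. So 4,500 women and 4,000 woman-years per arm reproduce with uncapped follow-up; 293 infections do not.

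**2. Infections required.**
- Schoenfeld: 4(1.960 + 1.282)² / (ln 0.67)² = 262 (263 rounded up).
- Freedman: (1.67/0.33)² × (1.960 + 1.282)² = 269 (270 rounded up).
- Power = Φ(½√D × |ln 0.67| − 1.960). With D = 293 this is 92.9%.

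**3. Woman-years available.** 5,000 × 1.5 = 7,500 with no loss. With follow-up uniform over 12–24 months and 7% annual loss, the model gives 6,907–6,937. This supports section 4, not the 8,000.

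**4. Infections and power for 5,000 women at 3.5%.** If 3.5% is the control rate and the 33% effect is real, the pooled rate is 3.5% × (1 + 0.67)/2 = 3.5% × 0.835.

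| Follow-up | 3.5% read as | Woman-years | Infections | Power |
|---|---|---|---|---|
| 12–24 months, mean 18, modelled | pooled | 6,907 | 242 | 87.5% |
| same | control | 6,937 | 203 | 81.3% |
| Section 4's 7,000 | pooled | 7,000 | 7,000 × 0.035 = 245 | 88.0% |
| same | control | 7,000 | 245 × 0.835 = 205 | 82% |
| 2-year accrual, 3-year study, 24-month cap | pooled | 7,952 | 278 | 91.6% |
| same | control | 7,993 | 233 | 86.4% |

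In the capped design, women recruited in year 1 have 24 months and those in year 2 average 18, so the mean is (24 + 18)/2 = 21 months. Reaching 293 at 3.5% needs 293/0.035 = 8,371 woman-years. Reaching it in 7,000 needs a pooled incidence of 293/7,000 = 4.2%.

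**5. Table 4.** Infections divided by (women × rate) give the years per woman used:
- Harare: 134/(2,200 × 0.04) = 134/88 = 1.52
- Durban: 99/(1,300 × 0.05) = 99/65 = 1.52
- Johannesburg: 60/(1,000 × 0.035) = 60/35 = 1.71

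At 1.52, Johannesburg would show 53, not 60. The rates are those the text gives for the control arm, but the column is headed as overall incidence and, at face value, applies them to all women, so the total contains no treatment effect.

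**6. Why the label on 3.5% matters.** The site-weighted control rate is 0.49 × 4 + 0.29 × 5 + 0.22 × 3.5 = 4.18%. Under a 33% effect the planned pooled rate is 4.18% × 0.835 = 3.49%. A pooled 3.5% would match the original plan; a control rate of 3.5% would be a real shortfall.

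**7. Interim looks.** Against 293, the looks at 100 and 195 fall at 34% and 67%. Against 245 they fall at 41% and 80%; against 278, at 36% and 70%.

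**The case against.** A reader might infer that no 12–24 month schedule can deliver the section 7.1.1 figures. The documents do not support that. Two-year accrual in a 3-year study with the 24-month cap keeps every woman within 12–24 months and gives 3,952 and 4,000 woman-years per arm, with 91.6% power if 3.5% is pooled. The conflict is with the 18-month mean and the 7,000 woman-years, and with 293, which this schedule also misses.

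A reader might also take 245 infections and 88% as the trial's true expectation. That combines section 4's woman-years with section 7.1.1's observed rate. Section 4 itself pairs 7,000 with 4%, giving 280 infections and 91.8%. That rate was a planning expectation, though, and section 7.1.1 reports a lower observed one. On the pooled reading, the gap to 90% is only about two points. The word overall suggests pooled but does not settle it.

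Nor can one conclude that 500 was the wrong increase. With uncapped follow-up and a 3.5% control rate, 5,000 women give 262 infections and 90.0% power, though with about 4,490 woman-years per arm rather than 4,000.

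On Table 4, one could suppose the treatment effect was built in. The implied years per woman then become 1.82, 1.82 and 2.05. The sites still disagree, and the last exceeds the 24-month cap.

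Finally, 293 errs on the safe side as a target. The looks are triggered by event counts and described as approximate, and the monitoring board may recommend more woman-years. This limits the harm but does not reconcile the figures.

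**Conclusion.** The point stands as a contradiction among the primary sample-size figures. At the stated 18-month mean, 8,000 woman-years cannot be reached, and 293 infections are not expected at 3.5%. Expected infections are 242–245 (power 87.5–88%) if 3.5% is pooled and 203–205 (81–82%) if it is the control rate. A 21-month mean restores about 4,000 woman-years per arm, with 278 infections (91.6%) or 233 (86%) on the two readings. In no case is 293 the requirement for 90% power, which is 262–269 before any small inflation for interim looks.

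These results assume constant hazards, 7% annual loss, a hazard ratio of 0.67 and uniform accrual. They do not show that the trial is seriously underpowered or that the interim looks are invalid. The size of any shortfall depends on two things the protocol leaves unsettled: the mean follow-up and what the 3.5% measures.

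**What to change.** - Use one follow-up assumption and one woman-year figure in sections 2, 4 and 7.
- State whether the April 2005 rate of 3.5% is pooled or control-arm, and make the incidence heading in Table 4 agree with the text.
- Recalculate Table 4 with the same years per woman at every site.
- State the required infections (262–269, before any inflation for interim looks) separately from the expected infections.
- Restate power with its assumptions: about 88% at 7,000 woman-years and 3.5% pooled; about 82% if 3.5% is the control rate; about 91–92% only with a 21-month mean and 3.5% pooled.
- In section 12.6, restate the information fractions of the 100- and 195-infection looks against the corrected target.

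This costs edits to the text and one table, and needs no extra women. The downside is that the stated power may be slightly less favourable.
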